#### Nicotine or sham nicotine patches

The nicotine or sham patch will be stuck on the chest, upper arm, wrist, or thigh of each participant, ensuring the patches are kept dry and clean. The specific course and dosage are shown (Table 2).

**Table 2 Tab2:** Duration and dosage of nicotine patch

Daily smoking/weight	Week 1-2	Weeks 3–4	Weeks 5–8
≥ 20	2 patches/day	1 patch/day	0.5 patches/day
< 20/≥70 kg	2 patches/day		
< 20/< 70 kg	1 patch/day		

### Baseline data

We will collect basic information including age, gender, ethnicity, educational level, BMI, blood pressure, heart rate, marital history, smoking history, daily smoking amount, times of quitting, smoking status of family members, and friends in the questionnaire.

### Outcomes

#### Primary outcome

Abstinence rate, relapse rate, and expiratory CO value will be selected as the main outcome indexes. The former two are mainly judged by the self-report of the participants at the end of treatment and follow-up, while the expiratory CO content is mainly detected by the CO detector.

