#### Secondary outcome

Secondary measures included a modified Fagerstrom test for nicotine dependence (FTND) score, a Minnesota Nicotine Withdrawal Scale (MNWS), and modified Brief Questionnaire of Smoking Urge (QSU-Brief) score. The three scores will be used to reflect the severity of nicotine dependence, withdrawal symptoms, and smoking craving of the participants. The higher scores indicate, the more severe symptoms. Each patient will be asked a questionnaire prior to the treatment and at 1, 4, and 8 weeks after the treatment. Table 3 shows the specific observation points of each index during the study.

**Table 3 Tab3:** The measurement time points of various indicators

Indicators	Before start of treatment	Treatment period			End of the follow-up
		Week 1	Week 4	Week 8	
Abstinence rate				√	√
Relapse rate					√
Expiratory CO value	√			√	
FTND scores	√	√	√	√	
MNWS	√	√	√	√	
QSU-Brief scores	√	√	√	√	

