### Data management and monitoring

We will collect the data by issuing questionnaires through WeChat in the form of “Questionnaire Star.” To enhance the accuracy of the data and maintain the quality of the data. All the data collected will be checked and collated by two dedicated data managers and then import into the Excel. These data will be kept confidentially until the end of the trial and will not be available to anyone except for the data administrator.

Our study will start in August 2021, and the specific study stages and procedures are shown in Fig. 1 and Table 1.

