## Discussion

Smoking is not only a physical dependence, but also a psychological dependence, thus, smoking cessation requires more than a strong will [21]. This study can only be carried out when the participants have certain intentions to quit smoking. We will choose two methods of NRT and acupuncture for the combined intervention of smokers who are willing to quit. Acupuncture is a relatively common and effective method in traditional Chinese medicine, while NRT is the most commonly used of the internationally recognized interventions. This combination is rarely reported in the literature, and it is expected to achieve better outcomes. We know that smoking behavior falls under the category of “mental and behavioral disorders resulting from the use of psychoactive substances” [22]. Thus, the choice of control group will not be a single intervention, but a combination of a placebo treatment of another method, as well as a group of pure placebo group. Each group will receive two interventions designed to blind the participants and provide a psychological cue that will help improve the effect of the intervention and promote participant compliance with the regulations.

There is a paradigm shift towards patient-centered care and active involvement of participants and public in research design and active participation throughout the research process [23]. However, to ensure the implementation of blind method in the later stage of the experiment, this paradigm has not adopted in the design of this study, and the protocol designers will be all composed of trial researchers, without the participation of the public or participants.

There are several limitations in the current study. First, although we chose the double dummy to try to blind the study participants, we are unable to blind the physicians, which may lead to some bias. However, all the subjective indicators are collected through the network background, which will minimize these biases to some extent. Secondly, although we have performed the sample size calculation, the sample size is still small, and a large sample test will be needed in the future stage.

Our study will evaluate the efficacy and safety of different interventions for smoking cessation, providing some evidence for smokers to choose smoking cessation programs, as well as for future studies, and promote the development of acupuncture for smoking cessation. The results will be published within 6 months after the trial completed.

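### Abstinence and relapse rest mainly on self-report: the exhaled CO scheduled at week 8 is not used to confirm a claim of quitting, and no CO is scheduled at end of follow-up

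*Protocol article*

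**What the plan says.** The Primary outcome section names three measures: "Abstinence rate, relapse rate, and expiratory CO value will be selected as the main outcome indexes". It then fixes how each is obtained. Of abstinence and relapse it says "The former two are mainly judged by the self-report of the participants at the end of treatment and follow-up", and it continues "while the expiratory CO content is mainly detected by the CO detector".

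The Secondary outcome section gives the timing: "Table 3 shows the specific observation points of each index during the study". In that table:

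- abstinence is assessed at week 8 and at end of follow-up;
- relapse is assessed at end of follow-up only;
- CO is measured before treatment and at week 8, not at end of follow-up.

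Data management and monitoring says that data come from an online questionnaire sent through WeChat. Blinding says that participants and data collectors are to be blinded and that practitioners cannot be. The Discussion repeats the last point as a limitation: "we are unable to blind the physicians, which may lead to some bias". It offers online collection of subjective measures as partial mitigation.

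The article gives no CO cut-off, does not make abstinence depend on CO, and does not say what happens when a participant's answer and the week-8 reading disagree.

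**The concern.** At week 8 the trial will hold both a participant's statement and a device reading on the same question, but the stated basis for the endpoint is mainly the statement. A continuing smoker who reports having quit is then a success. At end of follow-up there is no reading to compare with the answer.

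The damage depends on the pattern of misreporting. If continuing smokers in all arms over-report equally, every abstinence rate rises, the lowest rises most, and the contrast shrinks. If they over-report unequally, a difference can appear where none exists. Unequal reporting is a risk here because the practitioner who treats the participant knows the arm. Collecting answers online changes the channel; it does not verify the answer.

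**Working it through.** **Inputs.** From Sample size calculation: p1 = 0.56 (acupuncture), p2 = 0.091 (placebo), α = 0.05 with sidedness not stated, power 90%, at least 18 per group, 24 after a 30% loss allowance. The article gives no false-report rate, so the rates below are assumptions shown as a range.

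**The plan's own figure.** With p̄ = (0.56 + 0.091)/2 = 0.3255 and two-sided α:

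- 1.96 × √(2 × 0.3255 × 0.6745) = 1.96 × 0.6627 = 1.299
- 1.2816 × √(0.2464 + 0.0827) = 1.2816 × 0.5737 = 0.735
- N = (1.299 + 0.735)² / 0.469² = 4.137 / 0.220 = 18.8, so 19

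One-sided α gives 16. The stated 18 is within one of the two-sided result, and 18 × 1.30 = 23.4 rounds up to the stated 24. The sample size figure is not in dispute here.

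**Equal over-reporting, with 56% and 9.1% taken as true rates.** If a share f of continuing smokers claims to have quit, the observed rate is p + (1 − p)f. For f = 0.10:

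- acupuncture: 0.56 + 0.44 × 0.10 = 0.604
- placebo: 0.091 + 0.909 × 0.10 = 0.182

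Power is Φ{[Δ√n − 1.96√(2p̄(1 − p̄))] / √(p1(1 − p1) + p2(1 − p2))}. At n = 24:

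- f = 0: (2.298 − 1.299)/0.5737 = 1.74, power 0.959
- f = 0.10: (2.068 − 1.354)/0.6229 = 1.146, power 0.874

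| f | Observed rates | Difference (points) | Power, 24 per arm | Power, 18 per arm |
|---|---|---|---|---|
| 0 | 56.0% vs 9.1% | 46.9 | 0.959 | 0.886 |
| 5% | 58.2% vs 13.6% | 44.6 | 0.922 | 0.825 |
| 10% | 60.4% vs 18.2% | 42.2 | 0.874 | 0.759 |
| 20% | 64.8% vs 27.3% | 37.5 | 0.758 | 0.626 |
| 30% | 69.2% vs 36.4% | 32.8 | 0.632 | 0.505 |

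If the planned 30% are lost, 24 × 0.70 = 16.8, about 17 per arm remain. Power is then 0.866, 0.733 and 0.600 at f = 0, 10% and 20%.

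**Unequal over-reporting.** Let both arms have a true rate of 9.1%, with f = 20% in one and 10% in the other. Observed rates are 0.091 + 0.909 × 0.20 = 27.3% and 18.2%. This is a difference of 9.1 points with no true effect.

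**The other reading of the planning rates.** Suppose instead that 56% and 9.1% are self-reported and a share g of claims fails verification, so that the verified rate is p(1 − g).

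| g | Verified rates | Power, 24 per arm | N per group before loss |
|---|---|---|---|
| 10% | 50.4% vs 8.2% | 0.921 | 23 |
| 20% | 44.8% vs 7.3% | 0.866 | 27 |
| 30% | 39.2% vs 6.4% | 0.793 | 33 |

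On this reading over-reporting is already in the planning rates, so the power loss in the earlier table does not arise. The verified endpoint would instead have less power than planned.

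**The case against.** The best defence is that the article says abstinence is mainly, not solely, judged by self-report. A cut-off and a rule for discordant answers could also sit in a fuller document. That leaves room for a check, but the article does positively fix the self-report basis and a CO schedule that ends at week 8. A later analysis plan cannot verify follow-up status from a reading that was never scheduled.

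Four stronger readings are tempting, and the article does not support them.

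- **The trial ignores its objective measure.** It does not: CO is one of the three main outcomes. What is missing is its use to confirm abstinence.
- **A participant could succeed on one main outcome and fail on another.** CO is listed as a measured value with no cut-off, so nobody can fail on it. The gap is the lack of any rule linking the two.
- **Unblinded physicians coach participants differently by arm.** Participant's management system mentions verbal encouragement but does not say who gives it or tie it to arm. The schedule is the same for real and sham acupuncture, 3 × 4 + 2 × 4 = 20 sessions. Participants and data collectors are to be blinded and answers go in online. Unequal reporting remains a risk, not a demonstrated bias.
- **Power will fall to 0.87 or 0.76.** That holds only if the planning rates are true quit rates, and the article does not say whether they are.

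**Conclusion.** The concern holds in this form: abstinence and relapse are judged mainly by self-report, the week-8 CO is not tied to a claim of quitting, and follow-up status has no objective check. The direction of harm is dilution if misreporting is equal and possible spurious difference if it is not. The size is conditional. With 56% and 9.1% as true rates and 10% to 20% of continuing smokers claiming to have quit, power at 24 per arm falls from 0.96 to between 0.87 and 0.76. If those rates are already self-reported, that loss does not apply. Confidence is high that no confirming rule is stated; it is lower for the magnitude and for any difference in reporting between arms. The change should be made, because the week-8 reading it needs is already scheduled.

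**What to change.** Define week-8 abstinence as self-reported abstinence AND a week-8 exhaled CO below a cut-off fixed in advance for the detector in use. Count a missing or above-threshold CO as not abstinent. Keep the CO value and self-reported abstinence as supportive outcomes. Label abstinence and relapse at end of follow-up as self-report only wherever conclusions are drawn.

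This is more than a wording change. Statistical analysis uses a per-protocol set with last observation carried forward. The first would drop participants who do not complete. The second, if applied to week-8 CO, would carry forward the baseline reading. Neither counts a missing reading as not abstinent, so this endpoint must be exempted from both. Abstinence rates will be somewhat lower, and power against the planned rates may fall, as the last table above shows. Trial status says that recruitment is ongoing, so the change needs a documented amendment before unblinding. No new measurement is required.

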#### Secondary outcome

Secondary measures included a modified Fagerstrom test for nicotine dependence (FTND) score, a Minnesota Nicotine Withdrawal Scale (MNWS), and modified Brief Questionnaire of Smoking Urge (QSU-Brief) score. The three scores will be used to reflect the severity of nicotine dependence, withdrawal symptoms, and smoking craving of the participants. The higher scores indicate, the more severe symptoms. Each patient will be asked a questionnaire prior to the treatment and at 1, 4, and 8 weeks after the treatment. Table 3 shows the specific observation points of each index during the study.

**Table 3 Tab3:** The measurement time points of various indicators

Indicators	Before start of treatment	Treatment period			End of the follow-up
		Week 1	Week 4	Week 8	
Abstinence rate				√	√
Relapse rate					√
Expiratory CO value	√			√	
FTND scores	√	√	√	√	
MNWS	√	√	√	√	
QSU-Brief scores	√	√	√	√	

### Adverse events

Adverse events in this study included needle fainting, stagnation, bending, folding, and allergy during the use of the patch, as well as adverse reactions such as bleeding, hematoma, dizziness, fainting, residual needle sensation, tenderness, and infection during the treatment. In case of any adverse reaction, the physician will take protective measures for the subject in time and decide whether to stop the trial based on the disease condition and experience director. The study director will record the time, degree, duration, and treatment measures of the occurrence on the observation sheet and indicate the date of the report, to facilitate the later evaluation of the correlation between the occurrence and the test.

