## Introduction

Tobacco dependence is a chronic addictive disease, encoded as F17.21 in the International Classification of Diseases (ICD-10) [1]. Because cigarettes contain more than 70 carcinogens [2], long-term smokers can cause multi-organ and tissue damage, e.g., respiratory, cardiovascular, and neuromuscular diseases, and even death [3]. Quitting smoking is one of the most effective approaches to improve health condition and save lives. The benefit of reducing/quitting smoke is evidenced in improving the quality of life via decreasing the mortality and morbidity of cancer and cardiovascular diseases [4, 5]. Although there are 40% smokers who are/were willing to quit, only 8% are quitting successfully for multiple reasons [6]. Therefore, it becomes critical important to explore the effective approach to assist these remind unsuccessful quitting smokers to achieve their goal.

Nicotine replacement therapy (NRT), considered the basic treatment for smoking cessation, is the main pharmacological smoking cessation modality recommended by WHO [7]. Currently, NRT includes nicotine patches, nicotine gum, nicotine nasal sprays, and nicotine inhalers. Although nicotine patches are available for a long time within the most effective in smoking quitting [8, 9], the safety of nicotine patches is debated, partially is due to its adverse reactions, e.g., dizziness, headache, and nausea [10]. Acupuncture is a relatively common approach for smoking cessation over the past decades [11] with benefit of short-term abstinence, safety, and economic costs. During smoking cessation acupuncture significantly improves withdrawal symptoms, including upset, irritability, anxiety, and impatience experienced. However, the precise role of acupuncture for smoking cessation requires further clarification [12, 13]. Hyun S et al. demonstrate that NRT and behavioral counseling combined with auricular acupuncture are safer and more effective than traditional therapy alone [14]. However, it is still controversial about the efficacy of smoking cessation in acupuncture, NRT, and other interventions in clinical trials or related meta-analysis studies [15, 16], which remains to be validated.

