## Methods

### Objectives

The objective is to explore the effect and safety of different interventional approaches, e.g., acupuncture with or without nicotine patch, nicotine patch, and placebo for smoking cessation.

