### Sample size calculation

We will use the calculation formula of sample size of enumeration data in a completely random design, as describe previously. The PASS software will be used for calculation. The formula is listed as follow:$$N=\frac{\Big[{Z}_{\alpha}\sqrt{2p\left(1-p\right)}+{Z}_{\beta }{\sqrt{p_1\left(1-{p}_1\right)+{p}_2\left(1-{p}_2\right)\Big]}}^2}{{\left({p}_1-{p}_2\right)}^2}$$

*α* = 0.05 will be set up as the level of test, and the test power is 90%. The withdrawal rates of acupuncture (*p*_1_) and placebo (*p*_2_) will be 56% [18] and 9.1% [19], respectively; *p* is the mean of *p*_1_ and *p*_2_. The PASS 26.0 software will be used to calculate that the sample size required for each group for ≥18 cases. Considering 30% loss to follow-up rate, the sample size per group will be 24 cases. Consequently, the total number of the participants will be 96, based on 24 case per group in the four groups.

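### The adverse-event list does not name headache or nausea, two of the three patch reactions the Introduction cites, so they may be under-recorded

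*Protocol article*

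**What the plan says.** The Objectives section of the Protocol article sets out to "explore the effect and safety of different interventional approaches". The Introduction gives the reason the patch needs a safety assessment: "the safety of nicotine patches is debated, partially is due to its adverse reactions, e.g., dizziness, headache, and nausea".

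The Adverse events section lists the events in one sentence with two halves. The first half reads "Adverse events in this study included needle fainting, stagnation, bending, folding, and allergy during the use of the patch". The sentence then continues "as well as adverse reactions such as bleeding, hematoma, dizziness, fainting, residual needle sensation, tenderness, and infection during the treatment".

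Two statements on handling follow. On action: "In case of any adverse reaction, the physician will take protective measures for the subject in time". On documentation: "The study director will record the time, degree, duration, and treatment measures of the occurrence on the observation sheet".

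Under Sample size calculation, "the total number of the participants will be 96, based on 24 case per group in the four groups". Two groups receive the active patch (ACNP and SACNP) and two the sham patch (ACSNP and SACSNP). Every participant receives some form of needling and some form of patch.

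**The concern.** The Introduction names three patch reactions as the reason for doubt about the patch, and only one of them reaches the list of events the trial says it will look at. The rest of that list is detailed for needling and thin for the patch.

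The two kinds of event also come to light in different ways. A bent needle or a bleed is visible to the acupuncturist in the session. Headache and nausea are known only if the participant reports them. Leaving them unnamed adds to the chance that they are recorded less completely. The comparison at stake is active versus sham patch: if part of the true excess of these symptoms goes unrecorded, the difference between those groups shrinks, in a trial that intends to report on the safety of both treatments.

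**Working it through.** The plan states no figure that bears on this point, so there is none to reproduce. The check is a term-by-term comparison, followed by a short illustration of how incomplete recording acts.

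**1. Sort the named events.** The first half of the sentence has 5 terms and the second half has 7, so 5 + 7 = 12.

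| Origin | Terms | Count |
|---|---|---|
| Needling or needle site | stagnation, needle fainting, folding, bending, hematoma, bleeding, tenderness, infection, residual needle sensation | 9 |
| Patch only | allergy | 1 |
| Either treatment | fainting, dizziness | 2 |

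The allocation of single terms is a judgement (infection and tenderness are counted here with the needle site), but the balance is plain.

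**2. Compare with the Introduction.** Of its three patch reactions, dizziness is listed; headache and nausea are not. One of three is carried over.

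**3. Is the list closed?** The first half reads as a fixed list. The second half is introduced as examples. The next sentences refer to any adverse reaction and to recording the occurrence. No text confines recording to the 12 terms, so headache and nausea are recordable.

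**4. What would incomplete recording do?** Suppose the same fraction *c* of headache or nausea cases is recorded under active and sham patch. Then

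observed risk difference = *c* × true risk difference.

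There are 2 × 24 = 48 participants on active patch and 48 on sham patch. The documents give no event rates; those below are assumptions chosen only to show the mechanism.

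| Assumed true rate, active vs sham | c = 1 | c = 0.5 | c = 0 |
|---|---|---|---|
| 10% vs 5% | 5 points | 2.5 points | 0 |
| 20% vs 10% | 10 points | 5 points | 0 |
| 30% vs 10% | 20 points | 10 points | 0 |

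In the middle row, full recording gives an expected 48 × 0.20 = 9.6 and 48 × 0.10 = 4.8 cases. Half recording gives 4.8 and 2.4. The ratio stays at 2 but rests on half as many events. With full recording there is no bias. The document does not say what *c* would be.

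**The case against.** The strongest reply is that the section already allows for these symptoms. Its examples are only examples, action is tied to any adverse reaction, and no rule excludes headache or nausea. Dizziness is listed and is a patch reaction by the Introduction's own account. The design is double-dummy and one list serves all four groups, with participants and data collectors blinded, so the groups are not asked different questions. The observation sheet and the assessment schedule are not shown, and a journal article commonly leaves the method of eliciting events to the full protocol.

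Most of this stands, and it rules out several stronger readings:

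- A reader might infer that the patch groups will look safer than they are, or that the trial could find good tolerability because it never asked. The document supports neither, since it does not say the 12 terms are the checklist and does not restrict recording to them.
- A reader might multiply an assumed event rate by the 48 participants on active patch and call the product missed nicotine reactions. That assumes nothing is recorded and ignores the background rate under sham patch.
- A reader might take the references to the period of treatment or patch use as a strict cut-off that excludes late events. The wording is loose, and no cut-off for recording is stated.

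What the reply does not remove is the mismatch. The article does print a list, and that list omits two of the three reactions its own rationale rests on. The lack of a stated elicitation method is not the complaint.

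**Conclusion.** The point holds as a mismatch between two sections with a possible, unquantified effect on the safety comparison. It is certain that headache and nausea are cited in the Introduction and not named under Adverse events, and that the named events lean heavily to needling (9 of 12, against 1 specific to the patch). It is plausible but not established that unnamed, participant-reported symptoms would be recorded less fully than visible needling events. If they were, and equally so in both patch conditions, the active-versus-sham risk difference would be diluted in proportion. Any bias could lie anywhere from none to complete loss of that difference, depending on a recording fraction the document does not fix. The change is worth making because safety is a stated objective and the remedy is small. It does not call the design into question.

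**What to change.** Reconcile the Adverse events section with the Introduction:

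1. Add headache and nausea to the named events.
2. State that any untoward event after the first treatment is recorded, whatever its suspected cause, through the end of follow-up. This also settles the loose wording on timing.
3. Ask one short checklist, worded identically in all four groups, with the online questionnaires at weeks 1, 4 and 8 and at the end-of-follow-up contact. Putting it to the blinded participants also makes recording less dependent on the practitioners, who are not blinded.

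The cost is one reworded paragraph and a few extra items in questionnaires already being sent. The downside is slightly more burden and more non-specific events in every group; the sham-patch groups provide the background against which to read them. Recruitment is described as ongoing, so the date of the change should be logged. No dose, treatment or stopping rule is affected.
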